**Methods/design:**

This study will be conducted as a randomized, double-blind, placebo-controlled clinical trial for 12 weeks to receive daily β-CX 6 mg supplementation combined with a HPD on levels of metabolic factors, β-CX, glycemic and lipid profiles, inflammatory factors, adipocytokines, and body composition. Ninety-two eligible patients, aged 18–60 years, of both genders, who are obese and overweight (body mass index [BMI] 25–40 kg/m^2^) will be randomly assigned to four groups as follow: HPD + placebo; normal protein diet + β-CX (NPD + β-CX); HPD + β-CX; and NPD + placebo (control group). Two populations will be analyzed in this work. The intention-to-treat (ITT) population includes all patients who will be randomized, while the per-protocol (PP) population includes all individuals who complete the 12- week intervention (i.e. study completers).

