### Randomization and blinding

Each eligible patient will receive a randomization number which will be determined by a computer-generated schedule. A randomization table will then be generated by the method of random permuted blocks. Persons who will be operationally independent from the study investigator will perform the study randomization. The investigator, clinician prescriber, and patients will be blinded to the treatment condition. To maintain and guarantee blinding, β-CX and placebo will be identical in appearance. Also, all patients will be outpatients and none of the patients will be in contact with each other. Therefore, they cannot compare their diet. Patients’ data collected during this trial will be kept confidential and will be locked in a secure area. Randomization codes of the study will be opened only after all participants complete the study protocol. After the screening phase, participants will be assigned to four equal groups—HPD + placebo; NPD + β-CX; HPD + β-CX; and NPD + placebo (control group)—to receive an outpatient dietary regimen for 12 weeks. The supplements will be bought by Shanghai Tianfu Chemical Ltd. The study will be conducted in accordance with the ethical standards of the responsible Committee on Human Experimentation (institutional and regional) and the guidelines for the design, conduct, and reporting of human intervention studies [37].

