### Statistical analysis

Two populations will be used in the analyses. The intention-to-treat (ITT) population includes all patients who will be randomized, while the per-protocol (PP) population includes all individuals who complete the 12-week intervention (i.e. study completers). The data will be checked for plausibility by randomly checking the accuracy and completeness and verifying against source data. The variables will be tested for normality using the Kolmogorov–Smirnov test, the Shapiro–Wilk test, and normality plots. All quantitative data will be reported as mean ± standard deviation. Baseline characteristics of participants will be compared among groups using analysis of variance (ANOVA) for parametric data and the Kruskal–Wallis test for non-parametric data. The primary analysis, comparing the effects of treatment on primary outcomes of fatty liver over 12 weeks, will be conducted using a generalized linear mixed-models procedure. Treatments and time will be included as fixed effects and the interactions between interventions and time will be tested. If significant main effects or interaction effects are observed, post-hoc analysis with Bonferroni adjustments will be performed. Potential confounding factors and effect modifiers (e.g. baseline age and gender, etc.) will be investigated within the model. Logistic regression will be used to test the multiplicative interaction. Rothman’s synergy index, which would be equal to unity under additively, and less than unity when suggesting antagonism, will be utilized to examine the postulated interaction effect of a HPD and β-CX on fatty liver. The secondary analysis, comparing the effects of treatment on secondary outcomes of fatty liver over 12 weeks, will be conducted using the same procedure. Potential confounding factors and effect modifiers will be investigated within the model. Differences between participants who complete and withdraw from the trial will be analyzed using an independent t test or the Mann–Whitney test for continuous variables (e.g. age) and chi-square for categorical variables (e.g. gender). Associations between severity of fatty liver and nutritional status at baseline will be assessed using regression analysis. McNemar’s test will be used to analyze the binary variables before and after the intervention. Our statistical analyses will be performed by using SPSS 21 (IBM, Armonk, NY, USA) and the results will be considered significant at *P* < 0.05.

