### Sample size and sampling

The sample size was calculated based on the primary outcome measures (12-week change in serum adiponectin, CRP, FFA, insulin, serum β-CX, FBS). Using the standard deviations reported in previous studies [17, 20, 47, 48], a maximum sample size of 18 individuals per group will be selected with mean changes of adiponectin as much as 1.3 and standard division of 1.4 g/day and 30% attrition rate. It calculated by pass 11.

To achieve the target sample size, all patients who will come to the gastrology clinic of Ahvaz hospitals will be included in the study if they will be willing to participate in the study considering the inclusion criteria of the study.

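### The planned 92 patients, four equal groups, 18 per group and 30% attrition do not agree: 92 leaves about 16 per group after that loss

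*Protocol article*

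**What the plan says.** The Protocol article, under Sample size and sampling, says that "a maximum sample size of 18 individuals per group will be selected". The inputs listed with that figure are "mean changes of adiponectin as much as 1.3" and "standard division of 1.4 g/day and 30% attrition rate". The section does not say whether 18 is before or after attrition. It gives no power and no total, and it does not name the comparison.

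The total is in the Abstract, under Methods/design: "Ninety-two eligible patients". Under Randomization and blinding, "participants will be assigned to four equal groups". The step from 18 per group to 92 in total is not shown.

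The significance level is given under Statistical analysis: "the results will be considered significant at *P* < 0.05". Whether tests are one- or two-sided is not stated. The same section defines the per-protocol population as those who complete the 12 weeks. Under Primary outcome measures, serum adiponectin is in μg/mL, and fasting blood is drawn at admission and on day 85.

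**The concern.** Four numbers (92, four equal groups, 18 and 30%) should fit together under some reading of 18, and they do not. If 18 is the number wanted after losses, 92 is too few. If 18 is the number enrolled, 92 is too many.

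This is the article's only justification of trial size. Completers matter here because the primary blood outcomes are sampled at admission and day 85. A patient who leaves without a day-85 sample has no post-baseline value for them, even in an intention-to-treat analysis.

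A second, separate defect lies in the same sentence. The SD is given in g/day, but it belongs to a serum concentration. The SDs are said to come from several earlier studies, so the text alone does not show that 1.3 and 1.4 are on the same scale.

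**Working it through.** **Inputs from the Protocol article.** 18 per group; difference 1.3; SD 1.4; attrition 30% (Sample size and sampling). Total 92 (Abstract). Four equal groups (Randomization and blinding). Significance level 0.05 (Statistical analysis).

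**Assumptions of this check, not in the article.** Two-sided test, 80% power, comparison of two groups.

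**1. Reproducing the stated 18.** Normal approximation:

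n = 2 × (1.960 + 0.842)² × (1.4/1.3)² = 18.2 per group.

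The t-test version gives 19.2. Strict rounding up would give 19 or 20, so 18 is matched closely but not exactly. No attrition allowance is needed to reach it.

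**2. Enrolment per group.** 92/4 = 23.

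**3. What 23 leaves at the stated attrition.** 23 × 0.70 = 16.1 per group. In total, 92 × 0.70 = 64.4, against 4 × 18 = 72.

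**4. What keeping 18 would take.** 18/(1 − 0.30) = 25.7, so 26 per group and 26 × 4 = 104 in total. The plan is 104 − 92 = 12 short.

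**5. What loss 23 can absorb and still leave 18.** 1 − 18/23 = 0.217, about 22%.

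**6. The other reading: 18 already includes attrition.** Enrolment would be 4 × 18 = 72, not 92. Completers would be 18 × 0.70 = 12.6 per group, with pairwise power of about 61% (t-test) or 64% (normal approximation).

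**7. A probable origin of 92.** 18 × 1.30 = 23.4; taken as 23, 23 × 4 = 92. Rounding up would give 24 and 96, so the match depends on rounding down.

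**8. Effect on power.** Normal approximation: power = Φ(1.3 / (1.4 × √(2/n)) − 1.960).

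| Comparison | n per side | Normal approximation | t-test |
|---|---|---|---|
| One pairwise, stated n | 18 | 80% | 77% |
| One pairwise, 23 per group less 30% | 16 | 75% | 72% |
| Main effect, two groups pooled per side | 32 | 96% | 96% |

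The pairwise rows are two-sided 5% without multiplicity adjustment. The main-effect row assumes that the same difference of 1.3 and SD of 1.4 apply to the pooled comparison.

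**The case against.** The strongest case on the other side is that the article never promises 18 completers. It lists attrition beside the difference and the SD as if all three produced 18, so a literal reader may take 18 as already inflated. That can even be reproduced. If "mean changes of adiponectin as much as 1.3" meant a within-group change tested two-sided at 5% with 90% power, n = (1.960 + 1.282)² × (1.4/1.3)² = 12.2, and 12.2/0.70 = 17.4, which rounds up to 18. This point stands to the extent that the meaning of 18 is not settled by the text. It does not rescue the plan, because that reading implies 72 enrolled and leaves 92 unexplained.

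It is also fair to object that the multiplication by 1.30 is nowhere printed and works only with rounding down. A reader might treat it as established; the document supports it only as the likeliest explanation. The shortfall from 18 to 16.1 does not depend on it.

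The objection on consequence largely stands too. The design is a 2 × 2 factorial, the main analysis is a mixed model, and Bonferroni-adjusted comparisons come only post hoc. Main effects lose little power. A reader might infer that the trial as a whole is underpowered; the figures do not support that. A reader might also say that no significance level is given. In fact 0.05 is stated, and only power and sidedness are not.

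Finally, the g/day defect lends no weight to the attrition arithmetic. It is a separate correction.

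**Conclusion.** The concern holds as an inconsistency between stated figures. With 92 patients in four equal groups and 30% attrition, about 16 per group (64 in total) remain, not 18 (72). Neither reading of 18 gives 92: dividing by 0.70 gives 104, and taking 18 as enrolled gives 72. This rests only on numbers in the article.

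That 18 is a figure before attrition is the better-supported reading, but it depends on assuming 80% power and a two-sided 5% two-group comparison. The cause of the shortfall is inferred.

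The size is moderate: about five percentage points of power for a single unadjusted pairwise comparison, and almost none for the pooled main effects. The unit of the SD is wrong as printed. Both should be fixed; neither calls for a change of design.

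**What to change.** Keep 92. Restate Sample size and sampling so that it agrees with the Abstract: 92 randomised, 23 per group, giving about 16 completers per group at 30% attrition, or 18 per group only if attrition is at most about 22%.

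The authors should confirm whether 18 is before or after attrition and show how 92 was reached. They should also state the target power, the sidedness and the comparison it refers to (pairwise or factorial main effect). If they confirm a two-sided 5% unadjusted pairwise comparison, the power to report at 16 per group is about 72% by t-test (75% by normal approximation). If the target is a main effect, the pooled figure of about 96% applies under the same difference and SD.

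Replace g/day with the assay unit, after checking in the source studies that 1.3 and 1.4 are both 12-week changes in adiponectin on that scale. If they are not, the calculation has to be rerun.

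The cost is wording and a source check. No patients are added, and one stated planning figure becomes slightly less favourable.

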### Safety, adverse effects, and monitoring data

There are no side effects of 6 mg/d of β-CX supplementation [38, 39] and the recommended protein [17–20, 40]. This study will also monitor by a Data Monitoring Committee (DMC). All possible adverse events will also be reported to the Ethics Committee of the Ahvaz Jundishapur University of Medical Sciences. In addition, we will be monitoring compliance, gastrointestinal symptoms, and other adverse effects by phone calls and weekly meetings.

## Discussion

In addition to calorie restriction as the main role of reducing fat in the liver, manipulating of macronutrients and supplementation of micronutrients, especially antioxidants, as a part of lifestyle interventions may prevent the progression of fat accumulation in the liver and prevent NAFLD [49]. There is strong evidence from both experimental and animal studies suggesting that a low protein diet can lead to IR, high blood pressure, and lipid abnormalities, all of which are underlying mechanisms involved in NAFLD [50–52]; while dietary fat consumption may play a causative role in NAFLD [7, 53–56]. A HPD may lead to improvement in fatty liver but it has been poorly assessed and most of these studies are mainly limited to animal models [57]. However, well-controlled dietary intervention is limited [24, 58]. In addition to the HPD, β-CX is another component that we want to study in this work. β-CX is an antioxidant and may protect convert free-radical damage to biomolecules including lipids, proteins, and nucleic acids [26]. The β-CX is inversely associated with oxidative DNA damage, lipid peroxidation, and inflammation, GGT, and IR [30–35]. Of six carotenoids, only β-CX is inversely associated with type 2 diabetes [33].

According to the contradictory effects of β-CX and HPD on NAFLD, more long-term studies and clinical RCTs are needed to clarify the effects of carbohydrate restriction and β-CX supplementation on clinical outcome in patients with NAFLD. The findings will help physicians as a hugely important task to prevent the occurrence of NAFLD in people at risk and healthy individuals and will inform about the health impact of taking β-CX supplements and optimal dietary pattern to lose weight and thus avoid some chronic liver diseases. Finally, this study, as far as we are aware, will be the only study of its type to be conducted in Iran and one of the few studies conducted elsewhere in the world.

### Strengths and weaknesses

The main strength of this study is the double-blind placebo-controlled trial as a highest level of research evidence. Other strengths of the study may be listed as follows:There are no side effects of 6 mg/d of β-CX supplementation and we expect a high level of patient compliance in this study;Measurement of plasma metabolic parameters will suggest to clinicians the best treatment approach of β-CX supplementation and optimal dietary macronutrients distribution on weight loss, liver biochemistry, and IR in patients with NAFLD;We will measure the serum β-CX values by HPLC and its association with NAFLD;There are few studies of a HPD on NAFLD.

However, the high cost of a HPD and β-CX supplementation within 12 weeks and the likelihood of increased uric acid and other complications of a HPD may be the main weaknesses of this study.

## Trial status

This trial is in the ongoing phase.

## Abbreviations

ABSI: Body shape index
ALP: Alkaline phosphatase
ALT: Alanine transaminase
ANCOVA: Analysis of covariance
AST: Aspartate transaminase
BAI: Body adiposity index
BIA: Bioelectrical impendence analysis
BMI: Body mass index
CBC: Cell blood count
CR-HPD: Calorie-restricted high protein diet
DBP: Diastolic blood pressure
FBS: Fasting blood sugar
FFA: Free fatty acids
GGT: Gamma-glutamyl transferase
GPPAQ: General practice physical activity questionnaire
HDL: High-density lipoprotein cholesterol
HOMA-IR: Homoeostasis model-insulin resistance index
HPLC: High-performance liquid chromatography
ITT: Intention-to-treat
LDL: Low-density lipoprotein cholesterol
NAFLD: Non-alcoholic fatty liver disease
NASH: Non-alcoholic steatohepatitis
SBP: Systolic blood pressure
TG: Triglyceride
TNF-α: Tumor necrosis factor alpha
WHHR: Waist-to-hip-to-height ratio
WHR: Waist-to-hip ratio
WHtR: Waist-to-height ratio
β-CX: Beta-cryptoxanthin
